### Adherence

To maximize adherence to exercise in the intervention group, we will apply the core set of determinants for behavior change from Bandura’s Social Cognitive Theory: knowledge of health benefits, self-efficacy (expectations about the ability to perform the behavior successfully) and outcome expectations (perceived consequences of the behavior) [29]. Strategies to increase self-efficacy for physical activity will be evidence-based (i.e., vicarious experience and formalized comparative feedback) [30]. The Self-efficacy for Exercise (SEE) scale will be used to evaluate participants’ self-efficacy expectations of exercise expectations [31]. Throughout the trial, the kinesiologist will use motivational interviewing techniques to identify and reinforce the participant’s goals and reasons for changing behavior. To assess adherence and to provide additional motivation, the trial kinesiologist will phone intervention participants every 2 weeks in phase 2. To promote retention, all participants who complete the trial will be offered an additional counseling session with the study kinesiologist and an activity-tracking device. These incentives are intended to assist control-arm participants with increasing their levels of physical activity. For members of the intervention group, these incentives are intended to support the maintenance of physical activity levels.

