### Variables and their measurement

#### Baseline clinical information and study visits

A summary of the study schedule is shown in Table 1. Clinical data including cause of CKD, comorbidities, and medications will be collected via participant interviews, chart reviews, and reviews of clinical databases at the baseline study visit. Follow-up study visits are scheduled at 8 and 24-weeks. All participants will be contacted by phone every 2 weeks during the first 8 weeks of the trial to collect data on unscheduled visits and phone calls to healthcare providers, AEs, and changes to anti-hypertensive drugs. Over weeks 8 to 24, participants will be phoned every 4 weeks for this information. Data on AEs and medication changes will be verified using the electronic health repository.

**Table 1 Tab1:** Overview of trial outcomes by study visit

Outcome measure	Method	Baseline	Study visit 1 8 weeks	Study visit 3 24 weeks
Blood pressure	24-h ABPM Clinic BP with an automated oscillometric device	X	X	X
Anti-hypertensive dosing	Tabulated using the Defined Daily Dose (DDD)	X	X	X
Aortic stiffness	Pulse-wave velocity	X	X	X
Medication adherence	Questionnaire	X	X	X
Markers of cardiovascular risk Lipids, HgA_1_C, C-reactive protein Albuminuria, sodium intake Body composition	Blood samples Spot urine sample Bioimpedance spectroscopy, BMI	X	X	X
Cardiorespiratory fitness	Cardiopulmonary exercise testing Six-min Walk Test	X	X	X
Physical activity	7-day accelerometry IPAQ-SF	X	X	X
Quality of life	KDQoL-36 EQ-5D	X	X	X
Self-efficacy	Self-efficacy for Exercise scale	X	X	X
Adherence	7-day accelerometry Participant logbook		X	X
Adverse events	Self report and health record verification	X	X	X

Baseline data is collected prior to randomization. Adverse events are also collected by phone follow-up every 2 weeks for the first 8 weeks and every 4 weeks from weeks 8 to 24

Abbreviations: *ABPM* ambulatory blood pressure monitoring, *BMI* Body Mass Index, *BP* blood pressure, *EQ-5D* EuroQol Health Questionnaire, *HgA*_*1*_*C* hemoglobin A_1_C, *IPAQ-SF* International Physical Activity Questionnaire Short Form, *KDQoL-36* The Kidney Disease and Quality of Life Instrument*,*

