##### Adverse events

Adverse events (AEs) are defined as any unfavorable or unintended event affecting study participants. Major AEs include death, hospitalization (unplanned), emergency department visits, CV events (stroke, myocardial infarction); doubling of serum creatinine from baseline; permanent disability; syncope, arrhythmia. Minor AEs include symptomatic hypoglycemia, hyper- or hypotension requiring medical attention, musculoskeletal injury, pre-syncope during or within 1 h after exercise. Due to the low risk of the intervention we will not use a data safety and monitoring board. All serious adverse events will be forwarded to a physician who is not involved in the trial. The physician will adjudicate whether the event was due to the exercise treatment, facilitate the necessary medical follow-up, and determine whether participation should be modified.

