### Sample size

The sample size calculations for this trial are based on data from exercise and lifestyle modification trials in hypertensive populations [49–51]. As a 5-mmHg reduction in BP in high-risk patients reduces CV events by 15% [52], this study is powered to detect a clinically important difference in mean SBP of 5 mmHg between the intervention and the control groups. Using a two-sample *t* test, alpha 0.05, beta 0.2, and assuming a common standard deviation of 10 mmHg, 128 patients are required. Assuming 20% drop out, 160 patients will be enrolled (80 per group). This sample size is also powered to detect a clinically meaningful difference of 5 points in the KDQOL-36 (alpha 0.05, beta 0.2, and assuming a common standard deviation of 10 points) [53].

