### Statistical analysis

All analyses will follow the intent-to-treat principle. The difference in mean 24-h ambulatory SBP between groups at 8 weeks (primary outcome) will be analyzed using a mixed linear-regression model including fixed-effects terms for time point (8 weeks, 24 weeks), intervention, their interaction, baseline eGFR, baseline 24-h systolic ABPM, and a random-effects term for participant. In the primary analysis, missing values will be multiply imputed (100 iterations), using a hot-deck approach drawing all 8-week values from the control group with replacement, within strata of age and gender [54, 55]. Estimates from the 100 datasets will be combined using Rubin’s method [56]. Complete-case results, per-protocol and last-value-carried-forward results will be presented as sensitivity analyses. Estimates and corresponding 95% confidence intervals (CIs) will be reported for the overall difference at week 8 (and 24 weeks), adjusting for baseline eGFR and BP. All continuous outcomes with repeated measurements will be examined using mixed linear regression, following an outline similar to above. Continuous measurements without repeated measurements will be examined using linear regression, adjusting for baseline value. Residual, leverage and influence diagnostics will be examined. *P* values < 0.05 will be considered statistically significant. Adverse events will be tabulated, and compared between groups using Fisher’s exact test. All analyses will be completed in Stata/MP 15.1 (www.stata.com/).

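### The between-arm test of adverse events is open to bias against exercise for minor, self-reported events, because pre-syncope is defined by exercise and the exercise arm has more staff contact

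*Protocol article*

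**What the plan says.** **Test.** The Statistical analysis section of the protocol article states: "Adverse events will be tabulated, and compared between groups", and names Fisher's exact test for this. The general threshold in the same section is that "values < 0.05 will be considered statistically significant". The test is not limited to a class of event or a route of reporting.

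**Event definition.** The Adverse events section takes in any unfavourable or unintended event, then lists major and minor ones. Most major events (death, unplanned hospitalisation, emergency visits, stroke, myocardial infarction) normally leave a record. The minor list includes musculoskeletal injury and "pre-syncope during or within 1 h after exercise". No entry covers pre-syncope at other times.

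**Collection common to both arms.** Under Baseline clinical information and study visits, all participants are called every 2 weeks to week 8 about adverse events and other matters. After that: "Over weeks 8 to 24, participants will be phoned every 4 weeks for this information". Visits follow at weeks 8 and 24. Table 1 gives one method for everyone: self-report, verified in the health record.

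**Contacts in the exercise arm only.** The Exercise group section gives eight weekly supervised sessions in phase 1 and one kinesiologist visit in phase 2, plus others as needed. The Adherence section adds that "the trial kinesiologist will phone intervention participants every 2 weeks in phase 2". It describes those calls as serving adherence and motivation and does not mention adverse events.

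**The concern.** A between-arm test of harms is fair only if an event has the same chance of being counted in each arm. Two features work against this for minor events.

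First, the pre-syncope item depends on exposure to exercise. The same symptom in a control participant at an ordinary time of day is not a listed event, so the test of this item partly compares time at risk under the definition.

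Second, minor events surface when someone is there to hear of them. Staff at a supervised session see such events directly, while controls must recall them at calls 2 to 4 weeks apart. Participants are also unblinded (Randomization and blinding).

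Both features push towards an apparent excess with exercise. Adverse events are part of the secondary objective, and the tertiary objective is to inform a larger multi-center trial. A spurious harm signal could therefore carry into that trial's design.

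**Working it through.** **1. The plan's own figure, which gives the arm size.** The article gives no adverse-event rate and no power for adverse events. The only figure that can be recomputed is the primary sample size: "alpha 0.05, beta 0.2, and assuming a common standard deviation of 10 mmHg, 128 patients are required". For a difference of 5 and a standard deviation of 10, the two-sample t test needs 64 per arm, or 128 in total, and 128 / 0.8 = 160. This agrees with "Assuming 20% drop out, 160 patients will be enrolled (80 per group"). I use 80 per arm below.

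**2. Contacts, counted from the schedules.**
- Both arms: 8/2 = 4 calls to week 8, 16/4 = 4 calls in weeks 8 to 24, and 2 visits. Total 10, or 8 if the week-8 and week-24 calls merge with the visits.
- Exercise arm only: 8 supervised sessions + 1 phase 2 visit + 16/2 = 8 kinesiologist calls = 17.

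| Reading of the schedule | Exercise | Control | Ratio |
|---|---|---|---|
| All contacts separate | 27 | 10 | 2.7 |
| Calls at weeks 8 and 24 merged with visits | 25 | 8 | 3.1 |
| As above, no kinesiologist call at week 24 | 24 | 8 | 3.0 |
| Kinesiologist calls double as the 4-weekly calls | 23 | 10 | 2.3 |
| As above, and calls merged with visits | 21 | 8 | 2.6 |
| Contacts scheduled to collect adverse events | 8 to 10 | 8 to 10 | 1.0 |

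**3. The pre-syncope item.** The exercise arm is prescribed exercise on at least 3 days a week for 24 weeks, so 3 × 24 = 72 exercise days or more. Controls have none prescribed. Table 1 does not restrict the cardiopulmonary exercise test by arm, so each participant also has two tests after randomization. That gives at least 74 scheduled occasions on which pre-syncope can qualify in the exercise arm, against 2 in the control arm. If the item is counted almost only in the exercise arm, 6 of 80 against 0 of 80 is the smallest split that reaches significance (Fisher p = 0.028).

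**4. Unequal capture of minor events.** Let p be the true risk, equal in both arms. Suppose the exercise arm records every event and the control arm a fraction s of them. The probability of a false excess is the sum of Bin(a; 80, p) × Bin(b; 80, s·p) over all pairs with a > b and a two-sided Fisher p below 0.05. The documents give neither p nor s, so both are assumptions.

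| Relative capture s | p = 10% | p = 20% | p = 30% | p = 50% |
|---|---|---|---|---|
| 1.0 (equal) | 1.4% | 1.6% | 1.7% | 1.6% |
| 0.8 | 3.8% | 6.7% | 10.0% | 19.1% |
| 0.7 | 6.0% | 12.4% | 20.3% | 41.2% |

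With 64 per arm, s = 0.8 gives 2.8%, 5.5% and 8.1% for p of 10%, 20% and 30%.

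**The case against.** The strongest reply is that planned ascertainment is symmetric. Every participant gets the same adverse-event calls and visits, and Table 1 applies one method with record verification. The kinesiologist calls have another stated purpose. This stands. A reader might infer from the contact count that adverse events are sought three times as intensively with exercise, or that the test is biased as a matter of fact. The documents support neither: the ratio for scheduled collection is 1.0, and the size of any gap in capture is unknown. Verification does not close the matter for minor events, because as worded it confirms what was reported and does not clearly search for what was not.

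A reader might also infer that everything heard at exercise contacts is pooled into one test. The article does not say so. It does not exclude it either, and the test it states is unrestricted.

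On pre-syncope, the list is introduced as examples under a broad definition, so an episode away from exercise might count anyway. But the timing qualifier would then have no purpose. Pre-syncope during training is also a real harm, and counting it is not in itself bias. The fault is that the same symptom at other times is not listed.

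Larger error rates can be produced. With a true risk of 30% and detection of 90% against 60% or 50%, observed rates of 27% against 18% or 15% give a false excess in 22% or 40% of trials. Those inputs mean that controls capture only 67% or 56% of what the exercise arm captures, although they are asked every 2 to 4 weeks. Nothing in the documents supports gaps of that size.

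Finally, taking kinesiologist-reported events out of the only comparison could understate real exercise harms. This is a fair objection, and the fix allows for it.

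**Conclusion.** The point holds for minor, self-reported events. The difference in definition for pre-syncope stands in the text and needs no assumption about detection. The ascertainment part is a risk of unknown size, resting on 2.3 to 3.1 times as many total staff contacts with equal scheduled adverse-event collection. If controls capture 80% of what the exercise arm captures and true risks are 10% to 30%, the chance of a false excess rises from about 1.5% to about 4% to 10%. Those risks and that fraction are assumed. Most major events should be recorded in either arm, and their planned comparison is not in question.

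**What to change.** 1. For the between-arm comparison, count pre-syncope at any time in both arms.
2. Record for each event where it was first reported: common call, study visit, supervised session, kinesiologist contact or health record.
3. Keep the table of all events by arm. Base the p-value for minor events on those elicited at the common calls and study visits. Ask at each about everything since the last such contact, including anything already told to the kinesiologist.
4. Compare record-verified major events as planned.
5. Report events during or shortly after exercise sessions descriptively, for the exercise arm.

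The cost is one extra form field, a sentence or two in the analysis section and a little more tabulation. The minor-event comparison could miss exercise-arm events that are not repeated at a common contact, which is why the all-event table is kept beside it. No safety data are lost.

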#### Subgroup analyses

Using the model from the primary analysis, the relation between exercise and eGFR will be explored. Age and gender and corresponding treatment interactions will also be examined. Proteinuria will be considered in exploratory analyses. Changes in cardiorespiratory fitness and BMI as potential mediators of BP change will be explored.

### Data monitoring and quality assurance

Data will be entered directly at the site of data collection using tablets and an online RedCap database application. RedCap uses a secure syncing process and robust data validation techniques. The study coordinator will generate a weekly patient flow diagram reporting accrual, withdrawals, and fully completed protocols. The study coordinator will generate quality assurance logs containing information about participants’ missing or aberrant outcome testing and will then follow-up with the pertinent study personnel or participant.

## Discussion

Additional strategies to address the burden of hypertension in people with CKD are needed. Exercise is an appealing intervention due its proven efficacy in the general population and because of the potential for additional benefits. For renal healthcare providers, prescribing exercise to treat hypertension is a paradigm shift away from the mainstay of treatment, medication adjustment with or without dietary counseling on sodium intake. Therefore, to inform clinical decision-making on hypertension management in CKD, high-quality RCTs are needed to change practice. To our knowledge, this study is the first RCT designed to provide a precise estimate of the BP-lowering effect of exercise in people with moderate to severe CKD and hypertension. Strengths of this study include ABPM, which provides more accurate assessment of overall BP and kidney prognosis than clinic BPs [57, 58] and measurement of important confounders, such as anti-hypertensive dosing, medication adherence, and differences in physical activity levels between groups. Additional data on inflammation, vascular stiffness, and exercise recovery will improve our understanding of the CV response to exercise in people with hypertension and CKD.

This trial will also provide information on the effect of exercise on QoL as measured by the KDQoL. Developing care models that are more consistent with patient values and preferences and that address kidney-disease-specific symptoms (e.g., fatigue, low energy, depression) is a priority for decision-makers and patients [59, 60]. Exercise has improved several physical domains of QoL in people with CKD as measured with a generic instrument, but no trial has used a kidney-disease-specific tool [61, 62].

Towards the aim of designing a larger, multi-center trial to evaluate the effect of exercise on the progression of CKD, we will use the results from this current proposal to clarify trial processes, establish feasibility, and to estimate the variance of the treatment effect for eGFR. The need to identify lifestyle changes (e.g., exercise, reduced stress) that may delay kidney disease progression is an important question for patients [60]. The link between hypertension and renal function is well established and forms the scientific basis for first evaluating whether exercise can modify BP. Slower rates of eGFR decline were reported in a CKD cohort study comparing physically active people those who are sedentary (2.8% difference in annual eGFR decline) [63]. However, RCTs with adequate sample sizes and follow-up are needed.

## Abbreviations

ABPM: Ambulatory blood pressure monitoring
AE: Adverse event
BP: Blood pressure
CKD: Chronic kidney disease
CKD-EPI: Chronic Kidney Disease Epidemiology Collaboration
CPET: Cardiopulmonary exercise test
CV: Cardiovascular
DBP: Diastolic blood pressure
eGFR: Estimated glomerular filtration rate
EQ-5D: EuroQol Health Questionnaire
HgA_1_C: Hemoglobin A_1_C
KDQOL-36: The Kidney Disease and Quality of Life Instrument
PWV: Pulse-wave velocity
QoL: Quality of life
RCT: Randomized controlled trial
SBP: Systolic blood pressure
SEE scale: Self-efficacy for Exercise scale
VO_2_: Volume of oxygen consumption
